##### Economic Evaluation

###### Medical Consumption and Productivity Cost

Together with the intervention costs, such as the purchase of the social robot and subscription costs, medical consumption and productivity costs will be considered. To measure the medical consumption and productivity costs, a questionnaire containing relevant items from the iMTA Medical Cost Questionnaire and iMTA Assessment Productivity Cost Questionnaire will be conducted at baseline, effect, and follow-up [28,29]. These questionnaires are commonly used to study cost-effectiveness and can be adjusted by selecting relevant items.

###### Quality of Life

To measure the participants’ quality of life, the Icepop Capability Measure for Adults (ICECAP-A) will be administered [30,31]. The use of this questionnaire is advised when performing a cost-effectiveness study [32]. The ICECAP-A contains 5 items measuring stability, attachment, autonomy, achievement, and enjoyment.

Table 2 shows an overview of the measurements.

**Table 2 table2:** Study measurements overview.

Measurement	Baseline	Intervention adjustment	Effect	Follow-up	Used to answer RQ^a^
Daily registration of support (diary)^b^	✓	✓	✓	✓	RQ1 and RQ2
Weekly evaluation of goals (GAS^c^)^b^		✓	✓	✓	RQ3
Interview: well-being (PWI-ID^d^)^b^	✓	✓	✓	✓	RQ4
Interview: psychosocial impact (PIADS-10^e^)^f^			✓	✓	RQ4
Interview: added value of CiSR^f,g^			✓	✓	RQ4
Interview: work engagement and added value of CiSR^h^			✓	✓	RQ3, RQ4, and RQ5
Questionnaire: work engagement^h^			✓	✓	RQ5
Questionnaire: medical consumption and productivity cost (iMCQ^i^+iPCQ^j^)^b^	✓		✓	✓	RQ6 and RQ7
Questionnaire: quality of life (ICECAP-A^k^)^b^	✓		✓	✓	RQ6 and RQ7

^a^RQ: research question.

^b^Information on individuals with challenges in daily structure and planning, provided by the care professional.

^c^GAS: goal attainment scaling.

^d^PWI-ID: Personal Wellbeing Index–Intellectual Disability.

^e^PIADS-10: 10-item Psychosocial Impact of Assistive Devices Scale.

^f^Information on individuals with challenges in daily structure and planning provided by the individuals themselves.

^g^CiSR: care involving a social robot.

^h^Information on care professional.

^i^iMCQ: iMTA Assessment Medical Consumption Questionnaire.

^j^iPCQ: iMTA Assessment Productivity Cost Questionnaire.

^k^ICECAP-A: Icepop Capability Measure for Adults.

##### Analysis

###### Power

Due to the staggered design, power was determined through simulation using the R (R Foundation for Statistical Computing) packages simstudy and lme [33]. For a varying number of participants, 1000 datasets reflecting the staggered design were generated, all assuming a normally distributed outcome variable, a correlation between consecutive weeks of Pearson *r*=0.8, and a final effect of Cohen *d*=0.5 between the baseline phase and the first week of the effect phase (increasing linearly in 6 weeks). With 24 participants, a significant intervention effect (*P*<.05) was observed in 80.3% (803/1000) of cases, between the measurements from the baseline phase and those from the effect phase. Assuming 22% dropout (based on the study by van Dam et al [17]), the study is adequately powered when a total of 24 + (0.22 × 24) = 30 participants are included.

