### Study Design

A multiple baseline single case study will be conducted in everyday care practice. Multiple baseline single case studies are based on the principle that evidence of a causal effect can be strengthened by assigning participants to baselines of varying lengths. The staggered introduction of the intervention helps to rule out alternative explanations such as maturation or testing and session experience [20].

The study period consists of 3 phases (within 13 weeks) and a follow-up phase (Figure 1, Textbox 2, and Table 1). The number and timing of clusters is based on power calculations while considering the practical feasibility. The intervention does not allow for blinding within the trial.

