**Figure 1 figure1:**
[figure not shown]
Study planning overview. CAU: care as usual; CiSR: care involving a social robot.

Summary of the study period.Baseline phase: participants will be randomly allocated to 1 of 4 baseline lengths (2, 3, 4, and 5 weeks, respectively), resulting in 4 different clusters. In the baseline phase, participants will receive care as usual.Intervention adjustment phase: a 6-week phase in which each participant starts to receive compare care involving a social robot (CiSR), that is, using and adjusting to the social robot.Effect measurement phase: this period varies in length based on the cluster to which the participant is assigned, from 2 to 5 weeks. Participants will continue CiSR.Follow-up phase: to observe whether the results are maintained while participants continue CiSR, a follow-up measurement will take place 6 months after the start of the intervention adjustment phase.

**Table 1 table1:** Study planning.

Cluster	Baseline	Intervention	Effect	Follow-up	
1	2 weeks of CAU^a^	6 weeks of CiSR^b^	5 weeks of CiSR	Weeks 34-35	
2	3 weeks of CAU	6 weeks of CiSR	4 weeks of CiSR	Weeks 35-36	
3	4 weeks of CAU	6 weeks of CiSR	3 weeks of CiSR	Weeks 36-37	
4	5 weeks of CAU	6 weeks of CiSR	2 weeks of CiSR	Weeks 37-38	

^a^CAU: care as usual.

^b^CiSR: care involving a social robot.

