##### Effectiveness Study

Primary outcome data will be analyzed using a multilevel model (R, version 4.0+; package lme4) to investigate whether there is a significant difference between the level of professional care support moments (frequency or duration) per week in the baseline phase and the effect phase. The dependent continuous variable is the frequency and duration of professional care support moments per week. We will analyze all professional care support moments provided, as well as a selection of the specific professional care support moments connected to the goals for which the social robot is deployed.

The independent binary variable is the moment of measurement (baseline phase or effect phase). Because there are multiple measurements per participant at both phases, the model will contain a random intercept for participants. Time will be included in the model as a covariate. Measurements are consequently averaged and compared within participants per phase. Following the intention-to-treat principle, all participants will be included in the analysis, regardless of whether the participant has used the social robot in all weeks during the intervention adjustment phase and effect phase. Because multilevel models handle missing values well, no imputation is needed [34]. Quantitative secondary outcome data will be analyzed similarly. To assess the robustness of the primary outcome, additional per-protocol analyses and completers analyses will be performed as sensitivity analyses.

Clinical relevance will be determined per participant. Here, two conditions must be met as follows: (1) a Reliable Change Index of >1.96 for the level of support provided by care professionals [35] and (2) with CiSR, the participant progresses in carrying out the selected activities independently (GAS score of ≥+1 for at least one goal).

The follow-up data will be used to determine how many participants continue to receive CiSR, whether the effect is sustained in these participants, and what reasons there are to discontinue CiSR.

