### Strengths and Limitations

We describe the first adequately powered study that investigates the effectiveness and cost-effectiveness of using a social robot in daily residential care practice for individuals experiencing challenges with daily structure and planning. This study will give insight into the characteristics of participants for whom CiSR is successful by combining statistical and visual analysis and considering clinical relevance.

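### The 80.3% power figure does not match the primary model: if time is linear study week, 24 participants give roughly 17% to 38% power for d = 0.5

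*Protocol article*

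**What the plan says.** **Power.** The simulation assumes a normal outcome, a correlation of 0.8 between consecutive weeks, and an effect that builds linearly over 6 weeks to d = 0.5. With 24 participants, significance "was observed in 80.3% (803/1000) of cases, between the measurements from the baseline phase and those from the effect phase". The section does not say whether the model fitted to the simulated data had a time term, or how correlation behaves beyond adjacent weeks.

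**Effectiveness Study (analysis).** The primary model has a binary phase variable (baseline or effect) and a random intercept per participant. It continues: "Time will be included in the model as a covariate. Measurements are consequently averaged and compared within participants per phase". The coding of time is not given.

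**Study Design, Textbox 2 and Table 1.** Baseline lasts 2, 3, 4 or 5 weeks, then 6 adjustment weeks follow, and the effect phase fills the rest of the 13 weeks: "Effect measurement phase: this period varies in length based on the cluster to which the participant is assigned, from 2 to 5 weeks".

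**Claims that rest on these.** Study Design: "The staggered introduction of the intervention helps to rule out alternative explanations such as maturation or testing and session experience". Strengths and Limitations: "We describe the first adequately powered study that investigates the effectiveness and cost-effectiveness".

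**The concern.** The power statement and the primary model are given in adjacent sections as if they belong together. The contrast drops the six adjustment weeks, so no study week in the analysed data is observed under both conditions. A time covariate then competes directly with the phase variable, and the standard error of the phase effect should rise sharply. A simulation that kept 80% power at 24 participants is hard to square with that.

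Two things are at stake. If the model is fitted with study week, a true effect of the planned size would probably be missed, and a null result could be misread as absence of effect. If time is dropped to recover power, the primary result becomes a before-after contrast in which any drift, such as diary fatigue, counts as robot effect.

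**Working it through.** **Inputs.** From the protocol: N = 24; d = 0.5; lag-1 correlation 0.8; P < .05; phase lengths from Table 1; binary phase, random intercept and time as covariate. Assumed, because not stated: two-sided test, 6 participants per cluster, d on the total SD (set to 1), time as linear study week. The correlation structure is not stated either, so AR(1) and exchangeable were both run.

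**The plan's own figure.** 803/1000 = 80.3%, with Monte Carlo SE √(0.803 × 0.197/1000) = 1.3 points. Simulation noise cannot explain a large gap.

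**Geometry from Table 1.**

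| Cluster | Baseline weeks (mean) | Effect weeks (mean) | Gap | Within-phase sum of squares of week |
|---|---|---|---|---|
| 1 | 1-2 (1.5) | 9-13 (11.0) | 9.5 | 10.5 |
| 2 | 1-3 (2.0) | 10-13 (11.5) | 9.5 | 7.0 |
| 3 | 1-4 (2.5) | 11-13 (12.0) | 9.5 | 7.0 |
| 4 | 1-5 (3.0) | 12-13 (12.5) | 9.5 | 10.5 |

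Because the gap is the same in every cluster, the stagger gives no within-person contrast between phase and linear time. The slope has to come from inside the short phases and is then extrapolated over 9.5 weeks.

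**Hand check, exchangeable r = 0.8.**
- Residual variance = 1 − 0.8 = 0.2.
- Total within-phase sum of squares = 6 × (10.5 + 7 + 7 + 10.5) = 210.
- SE(slope) = √(0.2/210) = 0.031; times 9.5 = 0.293.
- SE of the phase contrast without time = 0.073.
- Combined: √(0.293² + 0.073²) ≈ 0.30; 0.5/0.30 ≈ 1.66; power ≈ Φ(1.66 − 1.96) ≈ 38%.

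**Model with linear study week, N = 24.**

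| Correlation | SE (generalised least squares) | Power | Simulated power, REML random intercept | Minimum detectable effect at 80% (2.80 × SE) |
|---|---|---|---|---|
| Exchangeable 0.8 | 0.300 | 38% | 37-39% | 0.84 SD |
| AR(1) 0.8 | 0.509 | 17% | 19-20% | 1.4 SD |

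If all 30 participants complete, simulated power is 46% and 21-22%. About 80% power would need roughly 64 to 72 participants (exchangeable) or about 200 (AR(1)).

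**Other readings of time.**
- *Categorical study week:* the phase indicator equals the sum of the indicators for weeks 9-13, so the phase effect is not estimable.
- *Phase means:* each participant has two values, always 9.5 weeks apart, so time and phase are fully aliased within person.
- *No time term, correctly specified covariance:* 58% under AR(1), about 100% under exchangeable. Random intercept plus AR(1) mixtures with lag-1 correlation 0.8 give 74% (intercept variance 0.33, ρ 0.7), 88% (0.5, 0.6) and about 95% (0.6, 0.5).
- *No time term, random intercept only, AR(1) data:* 85-87%, with type I error about 30%.
- *Time counted within phase, random intercept only:* 86-87% under AR(1) with type I error about 31%; about 100% under exchangeable.

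**Cost of leaving study week out.** A drift of 0.02 SD per week (illustrative) biases the contrast by 9.5 × 0.02 = 0.19 SD in every cluster.

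**The case against.** The strongest reply is that the protocol says only that time is a covariate. The coding may sit in an analysis plan that is not shown, so 17-38% is conditional on one reading. That stands. Week within phase would remove the power loss. It would not, however, adjust for a trend running across the study.

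Calendar time is a further reading. Locations start together within each organisation, but nothing says the three organisations start together. With assumed start offsets, no organisation effect and linear calendar week, power is 27-47% (4 weeks apart), 49-87% (13 weeks) or 55% to over 99% (26 weeks), with AR(1) at the lower end and exchangeable at the upper. This also stands, but the gain comes entirely from comparing organisations. Give each organisation its own intercept and calendar week becomes study week plus a constant, so the gain disappears.

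A reader might infer that 80.3% is a computing error. The documents do not support that. Valid baseline-versus-effect analyses without time run from 58% to about 100% depending on the correlation structure, so 80.3% may be right for a simulation that left time out.

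A reader might also infer that the stagger controls nothing. That goes too far: the protocol says only that it helps, and it plans visual analysis of each participant across all phases, where the stagger remains visible.

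**Conclusion.** The power statement and the primary model do not fit together as written. On the natural reading, linear study week, power for d = 0.5 with 24 participants is about 17-20% (AR(1)) to 38% (exchangeable), and the detectable effect is about 0.84 to 1.4 SD rather than 0.5. This rests on 6 participants per cluster, a two-sided 5% test and d on the total SD. If d were on the residual SD, exchangeable power with study week would fall to about 12%.

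The codings that keep power near 80% (time omitted or counted within phase) give up adjustment for a secular trend. With a random intercept alone and AR(1) data, they also reject a true null about 30% of the time. The claim of adequate power is therefore unsupported for the stated model. The finding is a mismatch between two sections. It does not prove that the trial's power is 17-38% under every coding the text allows.

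**What to change.** 1. State how time is coded and which within-person correlation structure the simulation and the model use.
2. Rerun the simulation with exactly the model to be fitted, including time and a residual correlation structure that holds type I error at 5%. Report power and type I error.
3. Replace 80.3% with the resulting power or minimum detectable effect, and revise the statement in Strengths and Limitations to match.
4. Delete the sentence on averaging per phase, or reconcile it with the weekly model.
5. Add, as a sensitivity analysis, a model on all 13 weeks with study week and an exposure term that is 0 at baseline, rises linearly over the adjustment weeks and is 1 in the effect phase. It uses weeks 3-5, when some clusters are on usual care and others on the robot.

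Item 5 should not replace the declared contrast, because it depends on the assumed ramp. Power is 68% (exchangeable) or 21% (AR(1)) if the full effect arrives in adjustment week 6, and 51% or 17% if it arrives in the first effect week.

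The cost is a rerun of an existing simulation and edited text, with no new data. The downside is a less favourable stated power. With 29 of 30 participants enrolled by October 2024, the realistic remedy is an honest statement of what the trial can detect.

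### The stated 80.3% power is not shown to apply to the time-adjusted primary model; if time is linear study week, power at d=0.5 is about 17-40%

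*Protocol article*

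**What the plan says.** **Power section.** One thousand datasets per sample size were simulated, with a normal outcome, "a correlation between consecutive weeks of Pearson *r*=0.8" and a standardised effect of 0.5 reached by the first effect week after a six-week linear rise. With 24 participants, significance "was observed in 80.3% (803/1000) of cases, between the measurements from the baseline phase and those from the effect phase". Allowing for 22% dropout, the section sets the sample at 30 and calls the study adequately powered. The fitted model is not given, and time is not mentioned as a term in it.

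**Analysis, Effectiveness Study section.** The primary model has a binary predictor (baseline or effect phase), a random intercept per participant and a time term: "Time will be included in the model as a covariate". The form of time is not stated. The section also says that measurements are averaged per phase, which leaves open whether weekly values or phase means are analysed.

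**Table 1 (Study Design).** Baselines last 2, 3, 4 or 5 weeks, each followed by 6 adjustment weeks and then 5, 4, 3 or 2 effect weeks.

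**Strengths and Limitations.** The power claim is repeated: "We describe the first adequately powered study".

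**The concern.** A power figure is useful only if it belongs to the test that will be run. The six adjustment weeks are outside the primary contrast. They leave a gap in every participant's series, so early weeks are all baseline and late weeks all effect. The stagger of at most three weeks does little to separate phase from calendar time. Adding time to the model should therefore cost a great deal of precision, and the Power section gives no sign that this cost was counted.

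The sample size and both claims of adequate power rest on this figure. If true power is far lower, a real effect of the planned size would usually be missed, and readers told that the study is adequately powered could take a non-significant result as evidence against the robot.

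**Working it through.** **Inputs.** From the documents: n=24, d=0.5, correlation 0.8 between consecutive weeks, normal outcome, the weeks in Table 1, binary phase, participant intercept and time covariate. Assumed: 6 participants per cluster, total SD 1, linear study week, weekly values from the baseline and effect phases only, and a two-sided 5% test. The decay of the correlation is not stated, so AR(1) and exchangeable structures were both run.

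**Step 1: trying to reproduce 80.3%.** Without time, n=24:

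| Analysis | AR(1) 0.8 | Exchangeable 0.8 |
|---|---|---|
| Random-intercept model | about 84-87% (type I error about 0.30-0.32) | about 100% |
| Paired t on phase means | 51-53% | about 100% |
| GLS, true covariance | 57.6% | about 100% |

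None gives 80.3%. The nearest, the random-intercept fit under AR(1), owes its high rejection rate partly to standard errors that ignore the serial correlation.

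**Step 2: overlap of phase and time.** Each participant contributes 7 analysed weeks. Within-participant sums of squares are:

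| Clusters | Phase | Week | Cross-product |
|---|---|---|---|
| 1 and 4 (each participant) | 2×5/7 = 1.429 | 139.43 | 13.571 |
| 2 and 3 (each participant) | 3×4/7 = 1.714 | 161.71 | 16.286 |
| Total, 6 per cluster | 37.71 | 3613.7 | 358.3 |

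- Correlation: 358.3/√(37.71×3613.7) = 0.971.
- Phase sum of squares left after adjusting for week: 37.71 − 358.3²/3613.7 = 2.19.
- Variance inflation: 37.71/2.19 = 17.2.

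The 17-fold figure applies where the random-intercept (exchangeable) structure holds. Under AR(1) with GLS the inflation is (0.509/0.232)² = 4.8, starting from a larger variance.

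**Step 3: power with time in the model.** Power = Φ(d/SE − 1.96) + Φ(−d/SE − 1.96). The detectable effect at 80% power is (1.96 + 0.84)×SE.

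| | AR(1) 0.8 | Exchangeable 0.8 |
|---|---|---|
| SE (GLS), n=24 | 0.509 | 0.300 |
| d/SE | 0.98 | 1.67 |
| Power, GLS | 16.6% | 38.4% |
| Power, simulated random-intercept fits | about 19% | about 38-40% |
| Detectable d at 80% power | 1.43 | 0.84 |
| Power with n=30, GLS | 19.6% | 46.1% |

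A hand check of the exchangeable case from within-participant information alone gives SE = √(0.2/2.19) = 0.302. Structures between the two extremes (random intercept plus AR(1), intercept share 0.5 or 0.7) give 19.3% and 25.5%.

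**Step 4: other forms of time and test, n=24.**
- Time since robot start: 17-19% (AR(1)) and 38-40% (exchangeable), much the same.
- Categorical week: no week holds both baseline and effect data, so the phase effect cannot be estimated.
- Week counted within phase: 86% under AR(1), with type I error about 0.31, or 100% under exchangeable correlation.
- One-sided test with linear week: 27% and 51%.
- All 13 weeks, exposure coded as a ramp, linear time, exchangeable correlation: about 68-70% two-sided and 79.7% one-sided.

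**The case against.** **The simulated model is not printed.** A reader might infer that the authors left time out of the simulation and that this explains 80.3%. The documents do not support that. The Power section says neither that time was in nor that it was out, and no variant without time reproduces the figure. This objection stands, and the source of 80.3% remains unknown.

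**The form of time is unstated, and it drives the result.** A reader might infer that no time-adjusted model could reach 80%. That is too strong. Week within phase restores high power, and the ramp-coded one-sided variant comes close to 80%. Neither rescues the plan as written. Week within phase does not adjust for a trend across the study, which is what the staggered baselines are meant to address. Ramp-coded exposure over all 13 weeks is not the binary baseline-or-effect contrast that the plan fixes. What stands is that the 17-40% range is conditional on linear time and must be labelled so.

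**Averaging.** Because the plan also speaks of averaging per phase, the weekly-value model is one reading of the text. That stands too, and the data level has to be settled before any rerun.

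**Interpretation does not rest on one P value.** The plan adds per-participant clinical relevance and visual analysis, and it nowhere says that a null result will be read as no effect. This softens the consequence but does not make the power figure right for the primary model.

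**Conclusion.** The power statement and the primary model do not fit together as written. Under the ordinary reading of the time covariate, a true d=0.5 is detected in about 17-19% (AR(1)) to 38-40% (exchangeable) of trials with 24 participants, and so missed in roughly 6 to 8 of 10. The full 30 without dropout raise this only to about 20-46%. The near-collinearity of 0.97 follows from Table 1 with equal clusters and linear time, and needs no assumption about effect size or correlation. The power range rests in addition on weekly values, a two-sided 5% test and the two correlation structures.

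This is a mismatch between the power basis and the analysis model. It is not a proven slip in the authors' simulation.

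**What to change.** 1. In the Effectiveness Study analysis section, state the form of the time term and that weekly values are the unit of analysis, and reconcile this with the sentence on averaging.
2. Rerun the simulation with that same model. State the correlation structure and check type I error under it.
3. Replace 80.3% by the power obtained, and state the detectable effect (about d=0.84 to 1.43 for 80% power if time is linear week).
4. Withdraw or qualify the claim of adequate power in the Power section and in Strengths and Limitations unless the rerun supports it.
5. State that a non-significant phase effect will be interpreted through its confidence interval.

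The cost is one rerun of the simulation and a few sentences of text. No extra enrolment is needed. The downside is a less favourable stated power.

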## Results

This project received approval for funding on July 13, 2023, by ZonMw, the Netherlands Organization for Health Research and Development (project 10310012210009). The funding period is 30 months.

Data collection from 30 individuals living in residential disability care organizations and the care professionals who provide them support will yield insights into the effectiveness and cost-effectiveness of CiSR. By October 2024, we had enrolled 29 participants. Data collection is planned to be finished in the third quarter of 2025. Data analysis will be performed from the second quarter of 2025. Results will be published in peer-reviewed journals and presented at international conferences in 2026.

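### The dropout allowance adds 22% of 24 instead of dividing 24 by 0.78, so 30 participants fall one short of the 31 needed to retain 24; the effect on power is small

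*Protocol article*

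**What the plan says.** The Power section reports a simulation of the staggered design with 1000 datasets for each sample size. The inputs given are "a final effect of Cohen *d*=0.5 between the baseline phase and the first week of the effect phase" and a week-to-week correlation of 0.8. The result is worded "With 24 participants, a significant intervention effect", at P<.05, "was observed in 80.3% (803/1000) of cases". The allowance for loss follows: "Assuming 22% dropout", a rate attributed to an explorative study of the same robot, leads to the statement that "the study is adequately powered when a total of 24 + (0.22 × 24) = 30 participants are included".

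The Abstract and the Results section use the same total of 30. Strengths and Limitations describes the study as adequately powered and as the first such study of its kind.

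The Effectiveness Study part of the Analysis section bears on what dropout costs. The primary multilevel model takes in every participant under intention-to-treat, without imputation. Completers and per-protocol analyses serve as sensitivity analyses.

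**The concern.** A dropout rate is ordinarily the fraction of enrolled participants who are lost. To end with 24, the number enrolled, N, must satisfy N × (1 − 0.22) ≥ 24. The article instead takes 22% of the 24 to be retained and adds it on, which always gives too small a total. The formula is printed, so the method does not have to be guessed.

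What is at stake is whether the stated total delivers the number it is meant to protect. The adequate-power claim rests on this line, and the simulated power at 24 is only just above 80%.

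**Working it through.** **Inputs**, all from the Power section: 24 participants required; power at 24 of 80.3% (803/1000); significance level 0.05, with sidedness not stated and two-sided assumed here; dropout 22%. The 80.3% is taken as given. The article does not describe the simulation model fully enough to confirm or refute it.

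**1. The article's own figure.** n × (1 + d) = 24 × 1.22 = 29.28, rounded up to 30. This reproduces the stated total. The sum allows for 5.28 losses, and 5.28/29.28 = 18% of those enrolled, not 22%.

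**2. Inflation for 22% of those enrolled.** n/(1 − d) = 24/0.78 = 30.77, rounded up to 31. Check: 31 × 0.78 = 24.18, which is at least 24.

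**3. What 30 delivers.** 30 × 0.78 = 23.4 expected to remain, 0.6 below target. The highest dropout that still leaves 24 is 1 − 24/30 = 20%, or 6 of 30. If participants drop out independently with probability 0.22 (an assumption), the chance that at least 24 remain is about 50% from 30 and about 63% from 31.

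**4. Effect on power.** Power of 80.3% at two-sided 0.05 corresponds to a standardised effect of 1.960 + 0.852 = 2.812. Scale this by the square root of the number retained:

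| Retained | Factor | Standardised effect | Minus 1.960 | Power |
|---|---|---|---|---|
| 24 | 1.000 | 2.812 | 0.852 | 80.3% |
| 23.4 | √(23.4/24) = 0.987 | 2.777 | 0.817 | 79.3% |
| 23 | √(23/24) = 0.979 | 2.753 | 0.793 | 78.6% |

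The loss is 1 to 2 percentage points.

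**5. Precision of the simulated figure.** The Monte Carlo standard error of 803/1000 is √(0.803 × 0.197/1000) = 1.26 points, so the 95% interval is about 77.8% to 82.8%. Both reduced figures lie inside it.

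**The case against.** The strongest reply is that the slip makes almost no difference. Rounding 29.28 up to 30 closes about half of the gap to 30.77 (0.72 of 1.49), which leaves one participant. The simulation cannot reliably separate 23 participants from 24. This stands, and it limits the point to a correction of the stated figure.

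The second reply is that the calculation treats dropouts as wholly lost, while the primary analysis does not. Someone who stops using the robot but still has diary entries stays in the model, and someone who leaves during the effect phase contributes baseline weeks and some effect weeks. This also stands, with a limit. The primary contrast is baseline against effect phase, and the effect phase starts only after 8 weeks (cluster 1: 2 + 6) to 11 weeks (cluster 4: 5 + 6). A participant who leaves before then supplies no effect-phase data, and the completers analysis feels the shortfall directly. The article does not define dropout, so 23.4 is best read as a pessimistic count of contributing participants.

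One could also argue that 22% was meant as losses relative to completers, which would make the printed sum right. Nothing in the text suggests that unusual meaning.

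Two stronger readings are tempting. A reader might infer that the study is underpowered because 80.3% leaves no room for error. That reads the simulated figure as more precise than 1000 datasets allow, and a fall to about 79% is not a material loss. A reader might also apply 22% to the enrolment figure in the Results section, "By October 2024, we had enrolled 29 participants", and get 29 × 0.78 = 22.6. That sentence reports progress at one date. The same section still refers to 30 individuals, and nothing says that recruitment closed at 29.

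**Conclusion.** The point holds as a wrong formula with a small consequence. At 22% dropout among those enrolled, 31 participants are needed to retain 24. The stated 30 leave an expected 23.4 and cover at most 20% dropout. Expected power at 22% dropout is about 79%, against the 80.3% quoted for 24, and the real loss is probably smaller because partial data are kept.

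This rests on four assumptions: 22% is a share of those enrolled; the test is two-sided at 0.05; power scales with the square root of the number retained; and the 80.3% is correct as stated. The point does not show material underpowering, and by itself gives no reason to change the design, the enrolment or the primary model. It is still worth correcting, because the article's claim of adequate power rests on this line and any reader can see that the sum does not protect the number it names.

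**What to change.** Replace the last sentence of the Power section with wording such as:

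> To retain 24 participants at 22% dropout, 24/(1 − 0.22) = 31 participants are needed. With 30 enrolled, 24 are retained if dropout is at most 20%; at 22% dropout the expected power is about 79%.

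Ideally the sponsor would take the power at 23 participants from its existing simulation, which was already run for a varying number of participants, in place of the square-root approximation. The cost is one line of text and a slightly less favourable power figure. No extra enrolment is needed.
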